**Table 6 Description of outcome measures**

| Outcome measure                       | Description                                                                                                                                      | Variable name | Presentation      | Value                    |                        |                        |                        |
|---------------------------------------|--------------------------------------------------------------------------------------------------------------------------------------------------|---------------|-------------------|--------------------------|------------------------|------------------------|------------------------|
| Primary outcome:               |                                                                                                                                                  |               |                   |                          |                        |                        |                        |
| Days of methamphetamine use           | TLFB days of methamphetamine use in the past four weeks (or since the last assessment date up to 35 days), with an offset for the days observed. | methdays      | Median (IQR) days | Baseline
24 (17 - 28) | Week 4
20 (12 - 26) | Week 8
18 (11 - 25) | Week 12
17 (9 - 24) |
|                                       | Days in observed period (offset used in analysis model)                                                                                          | methden       | Median (IQR) days | 28 (28 - 28)             | 28 (28 - 29)           | 28 (27 - 28)           | 28 (26 - 28)           |
| Secondary outcomes:            |                                                                                                                                                  |               |                   |                          |                        |                        |                        |
| Abstinence                            | Number of methamphetamine negative oral fluid samples (< 25 ng/mL)                                                                               | meth_positive | n (%)             | N/A                      | 31 (11%) a  | 33 (13%) a  | 36 (14%) a  |
| Depression (PHQ-9)                    | PHQ-9 score                                                                                                                                      |               | Median (IQR)      | 9 (4 - 13)               | 6 (3 - 10)             | 5 (2-9)                | 6 (2 - 9)              |
| Sleep (AIS-5)                         | AIS-5 score                                                                                                                                      |               | Median (IQR)      | 3 (0 -6)                 | 1 (0 - 3)              | 1 (0-3)                | 1 (0 - 4)              |
| HIV risk                              | HRBS score                                                                                                                                       |               | Median (IQR)      | 4 (2 - 8)                | 3 (1 - 6)              | 3 (1 - 6)              | 2 (1 - 6)              |
| Quality of life (EQ-5D)               | EQ-5D utility score                                                                                                                              |               | Median (IQR)      | 0.92 (0.85 - 0.97)       | 0.93 (0.85 - 1.00)     | 0.93 (0.85 - 1.00)     | 0.93 (0.89 - 1.00)     |
| Tertiary/exploratory outcomes: |                                                                                                                                                  |               |                   |                          |                        |                        |                        |
| Other substance use                   | Total days use for other drug classes (tobacco, alcohol, cannabis, cocaine, ecstasy, hallucinogens, inhalants, and heroin) in the past 28 days   |               | Mean (SD)         | 34 (20)                  | 31 (28 - 49)           | 31 (28 - 46)           | 30 (28 - 49)           |
| Suicidality                           | Score of 3 or more on the CSSRS-S since the previous assessment                                                                                  |               | n (%)             | 0 (0)                    | N/A                    | N/A                    | 11 (4)                 |
| Anxiety                               | Total score on the GAD-7                                                                                                                         |               | Median (IQR)      | 7 (3 - 12)               | 6 (2 - 11)             | 5 (2 - 10)             | 5 (1 - 10)             |
| Patient Impression                    | Patient Global Impression (PGI) scale score (range 1-7) b                                                                             |               | Mean (SD)         | N/A                      | 3.5 (0.9)              | 3.6 (0.9)              | 3.5 (1.2)              |

Notes. Data values are indicative only and may change with data cleaning. Inter-quartile range (IQR), standard deviation (SD), Timeline Followback (TLFB), Severity of Dependence Scale (SDS), Craving Experience Questionnaire (CEQ), Brief Psychiatric Rating Scale (BPRS)

aBased on data available at the time of writing this statistical analysis plan (797 oral fluid samples).

bA score of 4 represents no change. Scores lower than 4 represent a perceived improvement in health. Scores higher than 4 represent a perceived worsening of health.

## 5 Statistical Principles and definitions

### 5.1 Confidence intervals and p values

All tests will be two-tailed. Significance will be  $p < 0.05$  for all outcomes. Confidence intervals will be 95%.

### 5.2 Analysis populations

*The intention-to-treat (ITT) dataset* will include all randomised participants who received the trial medication (regardless of medication adherence or follow-up).

*The modified intention-to-treat analysis dataset* will include randomised participants who received the trial medication and who also completed at least one follow-up assessment at weeks 4, 8 or 12.

*The safety analysis dataset* will include randomised participants who received the trial medication and who completed at least one follow-up assessment at weeks 4, 8 or 12 (i.e., had some safety data).

*The Per-Protocol Analysis Dataset* will include randomised participants who received the intervention and for whom data was available for at least one follow-up assessment at weeks 4, 8 or 12. It will censor data for participants from the point from which they permanently discontinued medication if this was for reasons unrelated to the study medication.

*The Treatment Complier Analysis Dataset* will include participants in the Per-Protocol Analysis Dataset that censors assessment windows in the study if the medication adherence was below the median medication adherence for the study. The median medication adherence will be based on the ITT dataset for the total baseline to week 12 assessment period, excluding assessment windows when participants were discontinued from the medication.

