## 4.2 Screening and recruitment

A total of 1,267 participants were phone-screened for the trial (Figure 1). Of these prospective participants:

- 338 were not eligible based on the initial phone screening
- 29 did not complete the initial phone screening
- 900 were potentially eligible on the phone screen:
  - o 453 of these participants did not initiate a face-to-face eligibility assessment: 4 presented at the eligibility assessment but declined to consent; 1 presented to the eligibility assessment but was not consented to the study because they required acute health care; and, the remaining 448 were lost to follow-up (i.e., participants did not show for their eligibility assessment, wait-listed participants who could not be recontacted or were no longer interested in participating).
  - o 447 were consented to the study and started a face-to-face eligibility assessment: 368 were eligible, 58 were not eligible, and 21 did not complete the eligibility assessment (5 declined to continue with participation, 2 were in need of acute care, 1 assessment was terminated because the participant had no recent methamphetamine use, and 13 failed to show for their eligibility medical assessment).

Of the 368 eligible participants, 344 were randomised and 24 were not randomised (were lost to follow-up after eligibility or declined to participate).

Of the 344 randomised participants, 5 failed to attend their baseline assessment and hence did not receive the trial medication. Of the remaining 339 participants who received their trial medication, 20 participants did not attend any further assessments after baseline. Details of follow-up for the remaining participants can be found in Figure 1.

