## 4.7 Available assessment data

### Assessments attended

The number (%) of participants starting each assessment is shown in Table 3.

Five participants failed to complete their baseline assessment, and therefore did not receive the trial medication. These participants were not included in the intention-to-treat dataset.

Of the participants who completed their baseline assessment and were provided with the trial medication (N = 339), 315 (93%) started the week 4 assessment, 300 (89%) started the week 8 assessment, and 292 (86%) started the week 12 assessment. The overall follow-up of participants across the week 4, 8 and 12 assessments was 89% (907 of 1,014 assessments were started).

Week 2 adverse event assessments were completed on 320 of the 339 participants (94%) who received the trial medication.

Final data on the week 16 adverse event assessment, the final medical assessment, and the week 20 assessment were not available at the time of writing this statistical analysis plan.

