## 6.4 Planned analysis of the tertiary and exploratory outcomes

Planned analyses of the tertiary outcomes of other substance use, anxiety, and patient impression will be based on the unimputed intention-to-treat dataset.

Other substance use: The effect of the trial medication on days of other substance use will be tested using a mixed model with a group (placebo [0] vs. mirtazapine [1]) by time (baseline [0], week 4 [1], week 8 [2], week 12 [3], week 20 [4]) interaction effect, with time entered as a factor variable, producing individual effect estimates for each time point and making no assumptions about the linearity of changes over time. The primary timepoint is week 12. A generalised linear mixed model will be used to test this effect.

Anxiety: The effect of mirtazapine on anxiety will be tested using a mixed model using a group (placebo [0] vs. mirtazapine [1]) by time (baseline [0] vs. weeks 4 [1], week 8 [2] and 12 [3]) interaction effect, with time entered as a factor variable, producing individual effect estimates for each time point and making no assumptions about the linearity of changes over time. The primary timepoint is week 12. A generalised linear mixed model will be used to test this effect.

Patient impression: The effect of mirtazapine on the PGI scale score will be tested a group contrast (placebo [0] vs. mirtazapine [1]) across all follow-up time points (weeks 4, 8 and 12) to obtain an average treatment effect across the 12-week intervention period. A generalised linear mixed model will be used to test this effect.

Adverse events: The analysis of adverse event data will be based on the safety dataset and include only adverse event data for the 12-week trial medication period (wk 0 to wk 12). The percentage of participants reporting adverse events and serious adverse events for each System Organ Class will be compared between conditions using a Pearson's Chi-Square test. For serious adverse events, expectedness and causality will be reported.

Suicidality: The analysis of suicidality will be based on the safety dataset and include only suicidality data for the 12-week trial medication period (wk 0 to wk 12). The percentage of participants who screened positive for suicide risk (CSSRS-S score of 3 or greater) during the 12-week trial medication period (wk 0 to wk 12) will be compared between conditions (placebo [0] vs. mirtazapine [1]) using a Pearson's Chi-Square test.

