#### **Exploratory outcomes:**

5. *Adverse events (AEs):* Adverse events were assessed using open ended prompts about problems with the participant's health and problems with the study medication. All AEs were logged using a structured form that included information on date of onset and completion, severity, treatment received, relatedness to the trial medication, and whether the AE was a serious AE (SAE). AEs were assessed at week 2 after starting the trial medication; AEs were reviewed and updated at each assessment thereafter. AEs also include events that were identified outside this assessment process (e.g., at medical assessments) with these recorded at the nearest completed assessment. All AEs were coded by system organ classification according to the Medical Dictionary for Regulatory Activities (MedDRA)[30]
6. *Height and weight:* Self-reported height and weight were recorded at the week 12 assessment. Actual height and weight were re-assessed at the final medical assessment (week 18) when this was done in person.
7. *Treatment satisfaction* was assessed at week 12 using Treatment Satisfaction Questionnaire for Medication Version II (TSQM II) [27] which assesses medication convenience, side-effects and effectiveness for the previous 2-3 weeks (or since the participant had last used the medication, if

they had ceased medication). The TSQM II provides a global satisfaction summary score and subscale scores for medication convenience, side-effects, and effectiveness.

*Unpublished questions on medication tolerability:* Additional questions were included at weeks 4 and 8 to assess medication tolerability and adverse reactions to mirtazapine. These included a set of 5 generic questions about participants' perceived medication impacts and 7 questions specific to the expected effects of mirtazapine. These questions did not have a timeframe (they rated the participant's current beliefs and attitudes). At week 2 and week 16 a single question was included asking participants whether they had experienced any adverse reactions to mirtazapine, and withdrawal effects from ceasing mirtazapine, respectively. A final question asked participants whether the participant thought they were receiving the placebo (dummy pill) or active medication (mirtazapine) with the options of don't know, placebo (dummy pill), active medication (mirtazapine).

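### The safety set requires a week 4, 8 or 12 assessment, although adverse events are collected from week 2, so the harms comparison is conditioned on follow-up and can discard collected data

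*Combined protocol and SAP*

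**What the plan says.** Section 5.2 of the SAP defines the safety set as randomised participants who received trial medication and "who completed at least one follow-up assessment at weeks 4, 8 or 12 (i.e., had some safety data". The modified intention-to-treat set in the same section uses the same week 4, 8 or 12 rule. The intention-to-treat set does not: it "will include all randomised participants who received the trial medication (regardless of medication adherence or follow-up".

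The Appendix (Exploratory outcomes) describes collection: "AEs were assessed at week 2 after starting the trial medication; AEs were reviewed and updated at each assessment thereafter". It adds that "AEs also include events that were identified outside this assessment process", giving medical assessments as an example, and that these are entered at the nearest completed assessment.

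Section 4.7 gives the yield: "Week 2 adverse event assessments were completed on 320 of the 339 participants (94%) who received the trial medication". It also reports that "315 (93%) started the week 4 assessment, 300 (89%) started the week 8 assessment". Section 4.2 states that, of the 339 who received medication, "20 participants did not attend any further assessments after baseline".

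Section 6.4 uses the safety set for both adverse events and suicidality. The adverse-event comparison will "include only adverse event data for the 12-week trial medication period (wk 0 to wk 12"; suicidality has the same limit. Table 1 shows adverse events collected at weeks 16 and 20, with a physician review at week 18, and the suicidality screener repeated at week 20. The Appendix describes a week-16 question on withdrawal effects.

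**The concern.** The gloss in the safety-set definition treats a week 4, 8 or 12 assessment as the same thing as having safety data. By the SAP's own schedule it is not. Someone who reported a reaction at week 2 and never returned has safety data but is outside the set.

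Safety is half of the stated objective (section 2.2), and early exit can be related to tolerability. Section 4.4 gives adverse reactions among the reasons the study team stopped medication, and side-effects among the reasons participants did. A set defined by later attendance is conditioned on something that happens after randomisation and may depend on treatment. The harms analysis is then narrower than the efficacy analysis, which keeps every treated participant.

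A second, lesser matter is that data on the taper and post-treatment period are collected, but the SAP plans no by-arm display of them.

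**Working it through.** **Inputs.** Treated: 339 (sections 4.2 and 4.7). No assessment after baseline: 20 (section 4.2). Week-2 adverse-event assessments: 320 (section 4.7). Week-4 assessments started: 315 (section 4.7, Table 3).

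**The SAP's own figures.** 320/339 = 94.4%, stated as 94%. 315/339 = 92.9%, stated as 93%. Both reproduce.

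**How many fall outside the set.**
- Lower bound: the 20 with nothing after baseline cannot qualify. The set is at most 339 − 20 = 319, and 20/339 = 5.9% are out.
- Upper bound, on assessments started: anyone who started week 4 is in, so at most 339 − 315 = 24 are out, and 24/339 = 7.1%. Section 5.2 says completed rather than started, so the true number could be slightly higher.

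**How many of those excluded must have week-2 data.** With E excluded, the minimum is 320 − (339 − E) = E − 19.
- E = 20: at least 1.
- E = 24: at least 5.

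The most it could be is all E. If the section 4.2 statement was meant to cover week 2 as well, no more than 319 could have a week-2 assessment, and the 320 in section 4.7 contradicts it.

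**Effect on a reported percentage.** Take an assumed event proportion of 32/319 = 10.0% and restore 20 participants, k of whom had the event:

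| k | (32 + k)/339 |
|---|---|
| 0 | 9.4% |
| 1 | 9.7% |
| 2 | 10.0% |
| 3 | 10.3% |
| 20 | 15.3% |

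The break-even is k = 20 × 32/319 = 2.006. At this assumed rate the restricted percentage is too low only if three or more of the 20 had the event.

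**Chance that the 20 include any event of a given type.** 1 − (1 − p)^20 is 18% at an assumed risk of 1%, 56% at 4% and 88% at 10%. These risks are illustrative; the documents give no adverse-event rates.

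**Suicidality.** Table 1 has no suicidality screener at week 2. For that outcome the week 4, 8 or 12 rule does coincide with having on-treatment data, so the mismatch concerns adverse events.

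**Window.** Weeks 12 to 20 are 8 of the 20 weeks under observation. Section 3.6 places the final analysis after week 20, with adverse-event data in the locked database, so the later data will be available.

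**The case against.** **The count rests on a difference of one.** Section 4.7 has other small slips: week 12 is 292 in the text and 293 in Table 3, and assessments due are 1,014 in the text and 1,017 in the table. Read literally, section 4.2 says the 20 attended nothing at all after baseline, in which case 320 is a miscount and none of the 20 need have week-2 data. Unscheduled events are entered at the nearest completed assessment, which does not show that people with no later assessment have any. This stands as a caveat on the size. It does not rescue the definition, which would still exclude anyone with week-2 data alone.

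**A reader might infer that harms are under-reported.** The documents do not show it. Event counts can only be equal or lower under the restriction, but section 6.4 compares percentages, and the denominator shrinks too.

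**A reader might infer a bias favouring mirtazapine.** Neither the arm split nor the events of the 20 are given. The set depends on attendance, not on staying on drug, and 65 of the 85 who discontinued medication were followed up (section 4.4). Section 4.5 gives reasons for the 25 withdrawals, who are not necessarily the same people. None is labelled an adverse reaction, though two concern mental health.

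**The week 0 to 12 window is an explicit on-treatment choice.** Sections 6.2 and 6.3 note, for efficacy outcomes, that participants are offered off-label mirtazapine and other treatment before week 20. That muddies a late comparison by arm, and it is a good reason not to pool the periods. It is no reason to leave the later data undisplayed. The separate protocol may plan such a display (section 6.7 refers to it for exploratory analyses), but its text is not in the document reviewed.

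**A reader might infer that Pearson's chi-square is invalid for sparse events.** With 160 per arm, 4 v 0 gives p = 0.044 by chi-square and 0.12 by Fisher's test. But the exact size of the chi-square test at nominal 0.05 is 0.008 to 0.045 for event rates of 0.5% to 3%, against 0.0002 to 0.019 or 0.020 for Fisher's. The contrast mainly reflects Fisher's conservatism, and the choice of test is a preference.

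**Conclusion.** The safety-set definition should be corrected. It equates a week 4, 8 or 12 assessment with having safety data, and the SAP's own collection schedule contradicts that. Between 20 and about 24 of 339 treated participants (5.9% to 7.1%) are outside the set. At least one of them has week-2 adverse-event data, unless sections 4.2 and 4.7 are inconsistent, in which case those counts need correcting instead.

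The consequence is a harms comparison conditioned on follow-up, with the potential to discard collected data. The direction and size of any between-arm bias cannot be determined from the documents. The bounds assume that the counts are correct as printed and that starting an assessment approximates completing it.

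The week 0 to 12 restriction is a defensible main window. The absence of any planned by-arm display after week 12 is a smaller gap, worth filling descriptively.

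**What to change.** Before unblinding:

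1. Define the safety set as all 339 randomised participants who received trial medication, regardless of follow-up, and state that week-2 and unscheduled adverse events are included.
2. Report by arm how many had no post-baseline safety contact. Add a supporting table restricted to those with any such contact, week 2 included, because no-contact participants otherwise count as event-free and dilute the percentages. For the suicidality screener, which is not given at week 2, show the number assessed in each arm.
3. Reconcile sections 4.2 and 4.7: say whether the 20 attended week 2, and confirm the 320.
4. Keep weeks 0 to 12 as the main window. Add a separate descriptive by-arm table of adverse events, serious adverse events and CSSRS-S scores of 3 or more after week 12. For adverse events, show the taper period apart from the later period, when off-label mirtazapine is offered. The screener after week 12 is given only at week 20 and covers the time since the previous assessment, so it may not be separable in this way.

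The cost is SAP wording and a few tables from data already scheduled for collection. Section 6.1 says the plan was written on blinded data, so the change can be made without knowledge of allocation. The one statistical drawback, dilution by participants with no contact, is handled by the supporting table.
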